Our personalized targeting strategy aligns with the bimodal balance–recovery model of post-stroke rehabilitation (38). This framework proposes that functional recovery mechanisms are determined by the degree of structural reserve in the damaged hemisphere. When substantial white matter integrity is preserved (high structural reserve), recovery primarily occurs through remodeling of ipsilesional networks (interhemispheric competition model). Conversely, when structural damage is severe (low structural reserve), compensation predominantly relies on contralesional hemisphere recruitment (compensatory model). To operationalize this model clinically, we employ DTI to quantify the structural integrity of the left frontal aslant tract (FAT), thereby guiding individualized decisions to target either the ipsilesional or contralesional pre-SMA. Moreover, this trial specifically focuses on the early subacute phase (1–3 months post-stroke), which is recognized as a critical window for neuroplasticity and recovery. During this period, beneficial disinhibition and reorganization processes occur within motor and language networks, facilitating experience-dependent cortical remapping and responsiveness to neuromodulation (39–41). Selecting this time window is therefore intended to maximize the potential efficacy of individualized pre-SMA stimulation.

The current study has two primary objectives: (1) to determine whether fMRI-guided, individualized pre-SMA iTBS enhances language recovery in subacute PSA compared to sham stimulation, and (2) to characterize the neuroplastic mechanisms of treatment effects by examining pre-SMA-related circuit reorganization and functional connectivity changes within language network and domain-general cognitive networks. Our findings may establish a new precision medicine paradigm for aphasia rehabilitation that integrates connectivity-based targeting with biologically informed treatment protocols.

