## Data analysis

### Behavioral data

Repeated-measures ANOVAs are used to assess changes in WAB, BNT, NLCA scores, and speech parameters, with phase (pre- vs. post-treatment) as a within-subject factor and group (active vs. sham iTBS) as a between-subject factor. *Post hoc* comparisons are adjusted using the Bonferroni method. Data normality is checked with the Kolmogorov–Smirnov test; non-normally distributed variables are analyzed using the Wilcoxon signed-rank test. An intention-to-treat (ITT) approach is applied in the presence of missing data.

In cases where the assumptions of normality or homogeneity of variances are violated, a non-parametric Aligned Rank Transform (ART) ANOVA was applied to test for main and interaction effects. This approach preserves the interpretability of ANOVA-type models while providing robustness to deviations from normality. For *post-hoc* comparisons, the Wilcoxon signed-rank test (within-group) and Mann–Whitney *U*-test (between-group) are used with Bonferroni correction.

To further explore variability in treatment response, a sub-analysis will be performed within the non-fluent aphasia cohort, stratifying participants according to their baseline WAB-AQ scores to examine severity-related differences in iTBS efficacy. Participants will be categorized into mild (WAB-AQ: 50.4–93.7), moderate (30.1–50.3), and severe (0–30) aphasia groups based on their baseline scores (55). Changes in primary behavioral outcomes (WAB, BNT, NLCA) will be compared across these severity strata using mixed-design ANOVAs, followed by Bonferroni-corrected *post hoc* tests. This analysis aims to explore potential differential treatment responses across varying degrees of language impairment.

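### For non-normal outcomes the protocol gives two conflicting procedures without precedence, and one of them, the Wilcoxon signed-rank test, cannot compare active with sham

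*Protocol article*

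**What the plan says.** The first objective, in the Introduction, is "to determine whether fMRI-guided, individualized pre-SMA iTBS enhances language recovery in subacute PSA compared to sham stimulation".

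Under Data analysis, Behavioral data, the first paragraph sets the default: "Repeated-measures ANOVAs are used to assess changes in WAB, BNT, NLCA scores, and speech parameters". The model is a mixed one that crosses time with arm. The paragraph then adds a check, "Data normality is checked with the Kolmogorov–Smirnov test", and a consequence: "non-normally distributed variables are analyzed using the Wilcoxon signed-rank test".

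The second paragraph opens with a condition that includes the same one: "In cases where the assumptions of normality or homogeneity of variances are violated". The consequence there is different: "a non-parametric Aligned Rank Transform (ART) ANOVA was applied to test for main and interaction effects". For post hoc work that paragraph gives each rank test a role. It lists "the Wilcoxon signed-rank test (within-group" comparisons, and the Mann-Whitney U-test for comparisons between groups, with Bonferroni correction.

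No sentence says which paragraph governs when normality fails, or that the signed-rank sentence in the first paragraph covers only pre-post contrasts.

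**The concern.** The trial is a 1:1 parallel-group comparison with sham, so any test of efficacy has to contain the arm. The signed-rank test takes paired differences and asks whether they are centred on zero. Applied to a non-normal WAB score as the first paragraph directs, it returns a statement about change over time and none about iTBS.

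That matters in this population. Both arms receive a 30-minute session of speech and language therapy after stimulation (Treatment). Enrolment is at 1 to 3 months after stroke, which the Introduction describes as a critical period for recovery. Improvement in the active arm is therefore expected whether or not stimulation works.

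The second problem is that one trigger leads to two analyses. If normality fails for the WAB, either could be reported as the planned one, and they answer different questions.

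**Working it through.** **Step 1. Set the two rules side by side.**

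| | First paragraph | Second paragraph |
|---|---|---|
| Trigger | non-normality | non-normality or unequal variances |
| Procedure | Wilcoxon signed-rank | ART ANOVA, main and interaction effects |
| Contains the arm? | no | yes, through the interaction |
| Outcomes | WAB, BNT, NLCA, speech parameters | same section, no restriction |

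The second trigger is wider, but the two coincide on non-normality.

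**Step 2. What each test can see.** Let d = post minus pre for a participant. The contrast that objective 1 needs is mean(d, active) minus mean(d, sham). In the 2 × 2 mixed ANOVA this is the group-by-phase interaction. The signed-rank statistic is the sum of the ranks of |d| over participants with d > 0, and its null hypothesis is that d is symmetric about zero. The group label does not enter, whether the test is run within one arm or on both arms pooled.

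**Step 3. Illustration.** The protocol states no figure that depends on this rule, so there is none to reproduce. Inputs:
- 16 analysable participants per arm (Sample size estimation), with 20 enrolled per arm as a second setting.
- Two-sided 0.05 (same section).
- Assumption: normal change scores with SD 1 and the same mean change m in both arms, so the true active-sham difference is zero.
- Assumption: m from 0 to 1.0 SD. The protocol gives no value for m, so a range is shown.

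Results from 3,000 simulated trials per setting, 16 per arm, as % of trials significant:

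| m (SD of change) | Signed-rank, active arm | Signed-rank, arms pooled | Active significant, sham not | Mann-Whitney on change, between arms |
|---|---|---|---|---|
| 0 | 3.9 | 4.4 | 3.7 | 4.5 |
| 0.28 | 16.9 | 31.7 | 13.9 | 5.1 |
| 0.5 | 42.8 | 76.1 | 24.6 | 4.7 |
| 0.8 | 80.7 | 99.2 | 15.6 | 4.1 |
| 1.0 | 95.8 | >99.9 | 5.3 | 4.8 |

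A repeat with 4,000 trials gave 17%, 43% and 95% in the active arm at 0.28, 0.5 and 1.0 SD.

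Hand check on the fourth column: the arms are independent with the same rejection rate p, so it should be near p(1 − p). At m = 0.5 this is 0.428 × 0.572 = 0.245, against 0.246 simulated.

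With 20 per arm the active-arm signed-rank figures are 5.3%, 21.3%, 53.5%, 91.1% and 98.6%. Mann-Whitney on change stays between 4.4% and 5.4%.

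**Reading.** The signed-rank rate rises with the improvement the arms share, although the arms do not differ. The between-arm test holds its level. The ART ANOVA was not simulated.

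**The case against.** The strongest reply is that the second paragraph already does the right thing. It names an ART ANOVA with an interaction term, labels signed-rank as within-group, and assigns Mann-Whitney U to the between-group comparison. On that reading the first-paragraph sentence is a loose or leftover remark about paired comparisons. Nowhere does the protocol say that a significant within-arm change counts as efficacy. The data analysts are blinded (Blinding), which limits the scope for choosing the more favourable route, though it does not remove it.

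Most of this stands. A reader might infer that the plan lacks any non-parametric comparison of active with sham, and that would be wrong. What does not stand is that the conflict resolves itself. The first paragraph says non-normal variables are analysed with signed-rank and does not confine this to post hoc use. Nor can the conflict be left to a fuller document as missing detail, because the article states two incompatible rules.

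A reader might also infer that the Kolmogorov-Smirnov check is close to powerless at this sample size. The protocol does not support so general a claim, because it does not say which version is used or on which values. For exponential data, an uncorrected test with estimated mean and SD flags about 4% of samples of 20. With the Lilliefors correction the figure is about 58%, and uncorrected on 40 values it is about 23% to 24%. The criticism holds only for the uncorrected version at about 20 values, and the present point does not need it.

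Finally, the rates in the table are not the trial's false-positive rate. They use normal data, which are not the data that would trigger this route. They also apply only if the signed-rank branch is entered and its result is read as efficacy.

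**Conclusion.** The point holds in a limited form. The rule for non-normal outcomes is wrong as written: one of its two branches drops the randomised comparison, for the primary outcome among others, and the other branch conflicts with it with no stated order. This follows from the text and rests on no assumption.

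The size is illustrative. With no arm difference, 16 per arm and a common improvement of 0.28 to 1.0 SD of change, a signed-rank result in the active arm would be significant in about 17% to 95% of trials, against about 5% for a between-arm rank test of change. The common improvement and the normal shape are assumptions.

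The default group-by-phase ANOVA is untouched. A reader might infer that the primary model has to be replaced or the normality check removed, but this defect requires neither.

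**What to change.** 1. In the first paragraph of Behavioral data, delete the signed-rank sentence, or restrict it to within-arm post hoc description and say that such results are never evidence of efficacy.
2. Before unblinding, name one between-arm fallback for WAB-AQ. The smallest change is the group-by-phase interaction of the ART ANOVA already in the text. A Mann-Whitney test on change between arms would also do.
3. State the trigger once, so that non-normality leads to that one procedure. If the Kolmogorov-Smirnov check is kept, say which version is used and on which values.

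Optional: a baseline-adjusted model with a permutation p-value would give a between-arm test without a distributional switch. It is an alternative and is not needed to remove the contradiction.

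The cost is a few sentences of analysis wording. No data, visits or participants are affected.

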### fMRI preprocessing and functional connectivity analysis

The resting-state fMRI data are preprocessed using Statistical Parametric Mapping (SPM8; http://www.fil.ion.ucl.ac.uk/spm) and the Data Processing Assistant for Resting-State fMRI [DPARSF; (56)]. Preprocessing of the fMRI data involved the following steps: (1) discarding the first 10 volumes to allow signal stabilization and participant adaptation, leaving 190 images for analysis; (2) correcting for slice timing and head motion, with all participants exhibiting less than 2 mm displacement and 2° rotation; (3) co-registering T1-weighted images to the mean functional image and segmenting into gray matter, white matter, and cerebrospinal fluid; (4) regressing out confounding signals, including motion parameters and BOLD signals from ventricles and white matter; (5) normalizing functional images to MNI space using segmentation parameters (57), and resampling to 3-mm isotropic voxels; (6) smoothing with a 6-mm FWHM Gaussian kernel; and (7) applying temporal band-pass filtering (0.01–0.08 Hz) to remove low-frequency drift and high-frequency noise.

After the preprocessing, functional connectivity (FC) maps are calculated by computing Pearson correlation coefficients between the mean time series of each seed and all brain voxels, followed by conversion to Fisher *z*-values. Seed regions are defined as 6-mm-radius spheres centered at the ipsilesional pre-SMA (*x* = −4, *y* = 8, *z* = 50) and contralesional pre-SMA (*x* = 4, *y* = 8, *z* = 50), based on previous studies (10).

FC changes are analyzed at the voxel level using a 2 × 2 mixed-design repeated-measures ANOVA, with group (active vs. sham) as a between-subject factor and time (pre- vs. post-treatment) as a within-subject factor. Voxel-wise multiple comparisons are corrected using the false discovery rate (FDR, *p* < 0.05, cluster-level). *Post hoc* analyses further examine FC alterations within the pre-SMA–language network. Correlation analyses between FC changes and behavioral improvements are performed using Pearson correlation coefficients, with *p*-values FDR-corrected for multiple comparisons (*p* < 0.05).

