### Participants and recruitment

Participants will be recruited from Wuxi Central Rehabilitation Hospital. Eligibility requires meeting all of the following items: (1) a confirmed diagnosis of aphasia secondary to ischaemic stroke, with symptoms lasting between 1 and 3 months; (2) left-hemisphere ischaemic stroke confirmed by brain CT or MRI scan; (3) a first-ever stroke with a single lesion; (4) Aphasia Quotient (AQ) on the WAB < 93.8; (5) aged between 50 and 75 years; (6) native Mandarin speakers with at least primary school education; (7) right-handedness; (8) intact premorbid language function; (9) informed about the procedures of iTBS treatment and brain imaging scans, and provided written informed consent.

Given the focus of the current protocol, only patients with non-fluent aphasia (as classified by the WAB) will be included. The aphasia type of all enrolled participants will be determined and documented at baseline to ensure diagnostic accuracy and sample homogeneity.

Exclusion criteria include: (1) severe auditory, visual, or cognitive deficits limiting compliance; (2) significant dysarthria (NIHSS item 10 ≥ 2); (3) impaired consciousness (NIHSS item 1a ≥ 1); (4) major psychiatric disorders such as severe depression or anxiety that may interfere with participation; (5) aphasia due to other causes (e.g., brain tumor, traumatic brain injury, Parkinson's disease, motor neuron disease); (6) history of epilepsy or substance abuse; (7) contraindications to TMS or fMRI (e.g., scalp lesions, defects of the skull, intracranial implants, pacemakers, or drug pumps).

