### Lesion delineation and quantification

Stroke lesions were manually delineated on T2-weighted MRI images using MRIcron (https://www.nitrc.org/projects/mricron) by two trained raters and verified by a senior neuroradiologist. Lesion masks were normalized to MNI space to calculate lesion volume and the lesion–tract overlap ratio with the left frontal aslant tract (FAT). Both indices were included as covariates in statistical analyses to control for lesion-related effects.

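### The listed resting-state fMRI steps make no use of the lesion masks that the protocol already draws, so infarcted tissue can enter the white-matter regressor and is tested as brain in the voxel-wise connectivity analysis

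*Protocol article*

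**What the plan says.** Participants and recruitment requires a "left-hemisphere ischaemic stroke confirmed by brain CT or MRI scan", first-ever and single. Lesion delineation and quantification states that "Stroke lesions were manually delineated on T2-weighted MRI images using MRIcron", by two raters with verification by a senior neuroradiologist. Two uses of the result are given: "Lesion masks were normalized to MNI space to calculate lesion volume and the lesion–tract overlap ratio" with the left frontal aslant tract. The same section adds that "Both indices were included as covariates in statistical analyses to control for lesion-related effects".

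The section on fMRI preprocessing and functional connectivity then lists seven numbered steps. The ones that matter here are "segmenting into gray matter, white matter, and cerebrospinal fluid", "regressing out confounding signals, including motion parameters and BOLD signals from ventricles and white matter", and "normalizing functional images to MNI space using segmentation parameters", followed by resampling to 3 mm and smoothing at 6 mm FWHM. Connectivity is the correlation of each seed's mean time series with every voxel in the brain. The seeds are 6-mm-radius spheres at fixed coordinates, x = −4 and x = +4 (y = 8, z = 50). The maps go into a 2 × 2 group-by-time voxel-wise ANOVA, then post hoc analysis within the pre-SMA–language network and Pearson correlations with behavioural improvement. None of these steps names the lesion mask, and neither the ANOVA nor the correlations name a covariate.

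**The concern.** Segmentation into three normal tissue classes has no place for an infarct, so lesioned voxels must be assigned to one of them. Three consequences can follow.

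- Infarcted white matter can contribute to the white-matter signal that is regressed out of every voxel.
- A warp estimated from that segmentation may fit less well around the lesion.
- Because connectivity is mapped across the whole brain, infarcted voxels are tested as if they were functioning cortex.

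At stake is the second of the two main objectives in the Introduction, which concerns circuit reorganisation and connectivity change. The outcome section lists resting-state fMRI as secondary, and the WAB result does not depend on it. The post hoc work focuses on the language network. In left-hemisphere stroke with non-fluent aphasia, its left-sided nodes are likely to lie in or near the infarct.

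**Working it through.** **Following the mask through the pipeline.** The article gives no figure to reproduce here, so the check sets the sections side by side.

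| Stage | What the text states | Lesion mask mentioned? |
|---|---|---|
| Lesion volume and tract overlap | Computed from masks carried to MNI space | Yes |
| T1 segmentation | Three tissue classes | No |
| Nuisance regression | Motion, ventricles, white matter | No |
| Normalisation | From the segmentation parameters | No |
| Connectivity maps | Seed to every brain voxel | No |
| Voxel-wise ANOVA | Group × time | No |
| Correlation with behaviour | Pearson, FDR-corrected | No |

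The lesion covariates do not fill the gap. Lesion volume and tract overlap are one number each per participant. They can adjust a between-participant comparison, but they cannot remove infarct signal from a regressor, correct a warp, or make a lesioned voxel a valid observation.

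**Sensitivity of the seeds to misplacement (illustration only).** The inputs are r = 6 mm, from the seed definition, and an assumed displacement d, because the article gives no registration error. The share of a sphere that still overlaps its intended position is

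(4r + d)(2r − d)² / (16r³), with 16r³ = 16 × 216 = 3456.

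- d = 2 mm: 26 × 100 / 3456 = 0.752
- d = 3 mm: 27 × 81 / 3456 = 0.633
- d = 4 mm: 28 × 64 / 3456 = 0.519
- d = 5 mm: 29 × 49 / 3456 = 0.411

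So an error of one 3-mm analysis voxel would lose about 37% of the intended volume. This shows sensitivity. It does not show that such an error occurs.

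**Are the two seeds affected differently?** Their centres are 4 − (−4) = 8 mm apart. With d = 8 the same formula gives 32 × 16 / 3456 = 0.148, so the seeds already share about 15% of their volume. Each also crosses the midline. The cap has height h = 6 − 4 = 2 mm, and its share is h²(3r − h)/(4r³) = 4 × 16 / 864 = 0.074, or about 7%. A smooth warp error would move both seeds almost equally.

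**The case against.** **The argument is from silence.** The text is a journal article that condenses a fuller protocol, and the normalisation step cites a source whose handling of abnormal tissue cannot be judged here. That is fair, and it is why the point is confined to what the steps do when followed as written. It does not dispose of the point. The list is numbered and specific down to kernel width and filter band, and the whole-brain scope of the connectivity map is stated outright.

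**The damage is not shown.** This stands. A reader might infer that the seeds and maps are distorted by the infarct. The documents do not support that: lesion size and registration error are not given, the displacements above are assumed, and the Introduction says the pre-SMA is often preserved in left middle cerebral artery infarction. The overlap figures also overstate the loss of seed signal. Data acquired at 240/64 = 3.75 mm in-plane and smoothed at 6 mm share signal between neighbouring voxels.

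**The ipsilesional seed is not singled out.** A reader might expect it to suffer more than the contralesional one. With overlapping midline seeds, nothing in the documents supports this.

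**The CSF route is weak.** The regressor is ventricular signal, not all CSF, so a cortical lesion cavity is not clearly included. The white-matter route remains.

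**The treatment contrast is largely protected.** The same processing applies to both arms and both scans, and a lesion-related error that is stable over two weeks largely cancels in within-participant change. This stands for bias. It leaves noise, poorer localisation and the testing of infarcted voxels. It does not protect the correlations, which are not randomised comparisons. Lesion size could plausibly affect both the connectivity measure and recovery.

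**Conclusion.** The point holds in a limited form. The listed steps do not use the lesion masks in segmentation, normalisation, nuisance regression or the connectivity maps. As written, infarcted voxels can enter the white-matter regressor and are tested as brain, and normalisation near the lesion may be less accurate. The participant-level lesion covariates cannot correct any of this.

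The size cannot be stated from the documents. The exposure is greatest for infarcted and perilesional left-hemisphere targets in the language network, and less for the midline seeds. For the group-by-time contrast, expect mainly added noise and weaker localisation. For the correlations of connectivity change with behaviour, confounding by lesion size is also possible. It would go too far to conclude that the treatment comparison is biased or that stimulation is misdirected, since the target comes from individual mapping and not from these MNI seeds. The WAB is untouched.

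This rests on the numbered list being the pipeline that will actually be run. If the full protocol already masks the lesion, the remaining need is to say so.

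**What to change.** Amend the section on fMRI preprocessing and functional connectivity to state four things before data are analysed:

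1. The lesion mask is used in segmentation and normalisation, either by masking the lesion out or by filling it, with one method chosen in advance.
2. Each participant's lesion voxels are excluded from the white-matter and ventricle regressors, and from that participant's seed and connectivity maps.
3. The group ANOVA is restricted to voxels intact in a pre-set share of participants.
4. Seed placement is checked visually for each participant.

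The masks are already part of the plan, so this needs a script change, protocol wording and the visual check. It needs no new data and changes nothing for participants. The statistical price is that fewer voxels are tested in frequently lesioned areas, and the report should show which voxels were left out.

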## Methods

### Trial design

This investigation is designed as a prospective randomized controlled trial conducted at a single center, with a double-blind, sham-controlled structure. In total, 40 individuals with subacute PSA are enrolled from Wuxi Central Rehabilitation Hospital. The ethics approval number is WXMHCIRB2025LLky116, and the clinical registry number is ChiCTR2500108996. Participants are randomly allocated at a 1:1 ratio to either the real stimulation group or the sham stimulation group. Assessments are conducted on the enrollment day (T0) and following the completion of the iTBS intervention (T1), aphasia test batteries and fMRI are performed to evaluate language functions in PSA. Figure 1 illustrates the study design and data collection procedures, while Table 1 summarizes the timeline of enrolment and assessments.

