### Diffusion data analysis

All diffusion data are preprocessed offline using FSL 5.0.9 (https://fsl.fmrib.ox.ac.uk/fsl/fslwiki/FSL) (58). Preprocessing included correction for subject motion and eddy currents, with the b-matrix adjusted to account for rotational motion. Diffusion tensors are then estimated using nonlinear least squares fitting. Whole-brain tractography is conducted with a 2-mm uniform seed point resolution, applying termination criteria of FA < 0.2, angle < 30°, and fiber length < 50 mm.

The mean fractional anisotropy (FA) of the FAT is extracted to evaluate its microstructural integrity. FA reflects the directional dependency of water diffusion within fiber tracts, with values ranging between 0 (representing isotropic diffusion) and 1 (representing diffusion along a single direction), with higher values indicating greater fiber coherence and organization. FA is considered sensitive to microstructural properties such as myelination and axonal density, making it a useful marker for detecting subtle changes in white matter (59). FA values of the FAT are analyzed using a two-way mixed-design repeated-measures ANOVA, with group (active vs. sham) as a between-subject factor and time (pre- vs. post-treatment) as a within-subject factor. *Post hoc* pairwise comparisons receive Bonferroni correction. To assess structure–function–behavior relationships, correlations are computed between FA changes, FC alterations, and behavioral improvements using Pearson correlation analyses, with *p*-values FDR-corrected for multiple comparisons (*p* < 0.05).

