## Discussion

This randomized controlled clinical trial with a sham intervention aims to explore the neural and behavioral effects of personalized iTBS targeting the ipsilesional or contralesional pre-SMA. We hypothesize that stimulating the personalized pre-SMA with iTBS can enhance the effects of SLT on language recovery in PSA by modulating pre-SMA functional connectivity and inducing microstructural changes in the FAT, both of which are involved in language processing. The findings may offer evidence supporting the pre-SMA as a potential optimal stimulation target for treating subacute PSA. This study is designed to ascertain the integrity of the lesion-side FAT guided by DTI, and to carry out personalized intervention based on this. It is found that personalized pre-SMA iTBS stimulation might be a new neuromodulation approach for PSA recovery, as it is associated with the recovery of aphasia. Several studies indicate that rTMS has emerged as a potential therapeutic tool for ameliorating language dysfunction associated with PSA, yet the heterogeneity of treatment outcomes remains relatively high, which is attributed to variations in therapeutic targeting (60, 61). An extensive body of evidence indicates that the pre-SMA, as a specific target, is linked to the recovery process in patients with PSA, which further implies that it may serve as a potential stimulation target for cranial magnetic stimulation CMS interventions in PSA treatment (10). The development of fMRI-guided TMS-based personalized targeting for research may improve the therapeutic efficacy and therapeutic response rate of neuromodulation techniques, become an emerging means of stroke treatment, and be able to effectively reduce the burden of stroke patients' families and save social resources (62).

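### The correlations of FC and FA change with language change carry no arm term and none of the promised lesion covariates, so, if the arms are pooled, a treatment effect on both measures can appear as a brain–behaviour link

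*Protocol article*

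**What the plan says.** In the section on fMRI preprocessing and functional connectivity analysis: "Correlation analyses between FC changes and behavioral improvements are performed using Pearson correlation coefficients", with p-values "FDR-corrected for multiple comparisons". In Diffusion data analysis: "correlations are computed between FA changes, FC alterations, and behavioral improvements using Pearson correlation analyses", again with FDR. Neither section gives these correlations an arm term, a within-arm analysis or a covariate. Group enters only through the separate group-by-time ANOVAs.

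On lesion volume and the overlap of the lesion with the left FAT, Lesion delineation and quantification says: "Both indices were included as covariates in statistical analyses to control for lesion-related effects". None of the analyses under Behavioral data, the functional connectivity section or Diffusion data analysis mentions either index.

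The Introduction gives as the second of two primary objectives "to characterize the neuroplastic mechanisms of treatment effects by examining pre-SMA-related circuit reorganization", together with connectivity changes in language and domain-general networks. The Discussion hypothesises that iTBS enhances the effect of speech therapy on language "by modulating pre-SMA functional connectivity and inducing microstructural changes in the FAT".

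**The concern.** The trial's own hypothesis is that arm moves both variables being correlated. Pooling the arms then mixes two things: the difference between arm means, and the association among patients within an arm. Only the second says that patients whose circuits changed more also recovered more. The first is already tested by the ANOVAs, and it can make the pooled coefficient non-zero by itself.

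FDR does not help. It limits chance findings among true null hypotheses. Here the pooled correlation really is non-zero, because of arm, so FDR treats it as a genuine discovery.

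The lesion indices raise a similar problem. Lesion burden could plausibly influence FC change, FA change and recovery together, and the article says it is controlled for, but the stated coefficient does not do so. At stake is how the one analysis that ties circuit change to recovery is read.

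**Working it through.** **The plan's own figures.** The article gives no expected value, power or error rate for the correlations. Their sample follows from Sample size estimation: 16 per group evaluable, and 16/0.8 = 20 per group enrolled, so N is 32 to 40. Allocation is 1:1 (Trial design: "Participants are randomly allocated at a 1:1 ratio to either the real stimulation group or the sham stimulation group"). No arm difference is stated for FC or FA. For WAB-AQ the article assumes an effect size of 0.5 without naming its type. The arm differences below are therefore assumptions, shown over a range.

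One point helps in choosing the range for language. A standardised mean difference of 0.5 would need 63 (normal approximation) or 64 (t-test) per group. The stated 16 is approximately recovered if the arms differ by about 1 SD: n = 16 by the normal approximation, 17 by t-test. So 0.5 SD and 1 SD are both defensible for language. How the sample size was derived is a separate matter, and this point does not depend on it.

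**Pooled correlation with no within-arm link.** Let dx and dy be the arm differences in brain change and language change, in within-arm SDs, with zero correlation within each arm. Under 1:1 allocation the arm indicator has variance 1/4, so the covariance is dx·dy/4 and the variances are 1 + dx²/4 and 1 + dy²/4. Hence

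r = (dx·dy/4) / √[(1 + dx²/4)(1 + dy²/4)].

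- dx = dy = 0.5: 0.0625/1.0625 = 0.06
- dx = 1, dy = 0.5: 0.125/√(1.25 × 1.0625) = 0.11
- dx = dy = 1: 0.25/1.25 = 0.20
- dx = 1.5, dy = 1: 0.375/√(1.5625 × 1.25) = 0.27
- dx = 0 or dy = 0: r = 0

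**Rejection rates.** These come from 40,000 simulated trials per setting, one two-sided test at 0.05 with no multiplicity correction and no within-arm association.

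| dx, dy | Expected pooled r | Pearson, 16 per arm | Pearson, 20 per arm | Arm-adjusted, 16 / 20 per arm |
|---|---|---|---|---|
| 0, 0.5 | 0.00 | 5.0% | 5.0% | 4.9% / 4.9% |
| 0.5, 0.5 | 0.06 | 6.1% | 6.6% | 5.1% / 4.8% |
| 1, 0.5 | 0.11 | 9.3% | 10.2% | 5.0% / 5.0% |
| 1, 1 | 0.20 | 20.3% | 24.1% | 5.3% / 5.1% |
| 1.5, 1 | 0.27 | 32.8% | 41.1% | 5.0% / 5.2% |

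The pooled rate rises with sample size because the pooled correlation is truly non-zero. Adjusting for arm keeps it near 5% in every setting.

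**Lesion indices.** Suppose a lesion index correlates b with both changes and nothing else links them. The unadjusted correlation is then about b². The values of b are assumed. At 16 to 20 per arm, b = 0.3 gives r of about 0.09 and about 8% rejections; b = 0.4 gives 0.16 and 14% to 16%; b = 0.5 gives 0.25 and 29% to 35%.

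**Degrees of freedom.** With N = 32 a plain Pearson test has 32 − 2 = 30. Adjusting for arm and two lesion indices leaves 32 − 5 = 27.

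**The case against.** **Pooling is inferred.** Neither section says whether the arms are combined. Correlations run strictly within each arm would remove the arm problem, and a condensed article may leave the analysis sample to a fuller document. This stands as a limit on the claim. It does not dispose of it, because the article does fix the method, and that method as worded has no arm term.

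**The size is assumed.** At 0.5 SD on both measures the distortion is negligible. The 20% and 33% figures need FC or FA differences of 1 to 1.5 SD, which the article does not give. They also describe one uncorrected test. A reader might infer that these are error rates of the planned FDR-controlled analysis; they are not.

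**The second objective does not rest on these correlations.** A reader might infer that a primary objective is undermined. The objective concerns circuit and connectivity change, which the group-by-time ANOVAs test with an explicit arm factor, and its wording does not mention brain–behaviour correlation. The correlations are supportive. It remains true that no other planned analysis links circuit change to recovery.

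**The lesion gap is not specific to the correlations.** The ANOVA descriptions also omit the indices, and the general statement on covariates could be meant to cover everything. A Pearson coefficient computed on covariate-adjusted residuals would be a partial correlation. But the article does not describe that, so the sections need reconciling.

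**A marginal correlation is a legitimate description.** That is so, but a study of the mechanisms of treatment effects invites a patient-level reading, which the pooled coefficient cannot support.

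**Conclusion.** The point holds in a limited form. As worded, the correlations have no arm term. If they are computed across both arms, and if iTBS shifts both the brain measure and language as the Discussion hypothesises, they will show an association that need not exist within either arm. The size runs from nil (either arm difference zero), through r of about 0.06 and 6% rejections (0.5 SD in both), to r of about 0.20 and 20% (1 SD in both, N = 32). These figures rest on pooling, on assumed arm differences, and on a single uncorrected test.

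Separately, and whether or not the arms are pooled, the statement that the lesion indices are covariates is not carried through to any described analysis. The documents do not support saying that the protocol states pooling, that the covariate gap is peculiar to the correlations, or that the second objective fails. The change is nevertheless worth making before analysis: it uses data already collected, and it protects the only analysis that joins circuit change to recovery.

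**What to change.** In both the functional connectivity section and Diffusion data analysis, replace the Pearson correlation with a partial correlation, or a regression of language change on FC or FA change, adjusted for arm, lesion volume and lesion–FAT overlap. Where FA change is correlated with FC change, use the same adjustment. Keep the FDR correction. State that both arms are included, and show the within-arm correlations descriptively. Baseline WAB-AQ may be added, but this is optional, since the article does not name it as a covariate.

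Also state in Lesion delineation and quantification which analyses carry the two lesion indices, so that it agrees with the ANOVA descriptions as well as with the correlations.

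The cost is a change of wording and about three degrees of freedom (30 to 27 at N = 32). Reported correlations may be smaller, because the part due to the arm difference is removed.
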